### Who will take informed consent? {26a}

Participants meeting the inclusion criteria will be invited to participate via email. With this invitation email, they will receive the detailed study information letter and the informed consent sheet and will be invited to schedule an online enrollment meeting via Microsoft Teams. At the enrollment meeting, the researcher will verbally explain the study. This will include the schedule and activities as well as the timeline for online surveys and the optional interview. The researcher will give the participants a chance to ask questions, and then, if the participants are ready, they will digitally sign the informed consent sheet. A follow-up meeting will be scheduled if the participant needs more time to consider joining the study. The informed consent and info sheet provide information about the storage and protection of the data and the right to leave the study at any time. The time-stamped digital informed consent will be kept according to the GDPR art.6.1.a.

### Additional consent provisions for collection and use of participant data and biological specimens {26b}

No biological specimens will be collected.

## Interventions

### Explanation for the choice of comparators {6b}

The intervention and control conditions are described in detail in Table 1, including the intervention goals, activity descriptions, and duration. Both programmes are designed to be progressive curriculums that build upon each day. All intervention programme components were selected based on previous research and have been pilot-tested. The objectives of the intervention programme (see also Table 1) are to help individuals develop an aesthetic mindset, practice observation and appreciation skills, apply these skills to their day-to-day lives, practice emotion regulation with beauty, and incorporate more beauty into their lives. The programme aims to facilitate a gradual transfer of skill from appreciation in art contexts to natural beauty and everyday life. On the other hand, the control programme is designed to match the intervention programme in all aspects except for teaching beauty appreciation and increasing exposure to art and beauty. Past studies [15, 16, 18] have not included control over increased observation skills as a possible confounding factor; instead, other studies have used active control conditions but not matched conditions that truly isolate beauty appreciation as a learned skill or behaviour.

**Table 1 Tab1:** Intervention and control condition programme descriptions

	**Intervention**		**Control**	**Time (mins/day)**
	**Goal**	**Activity description**	**Equivalent activities**	
**Day 1**	Develop Aesthetic Mindset Practice Aes. Mindset and observation skills	4-minute priming video showing a landscape painting that focuses on the brushstrokes, composition, and colour Museum visit with audio guide and reflection about visit. Audio guide asking participants to slow-look at 1–3 artworks and reflect on the meaning and beauty	Priming video about learning to pay attention and being observant in everyday life Visit to be a tourist in their own city or a new city with an audio guide with directions to focus on counting things like pedestrians, types of buildings, details	120
**Day 2,3,4**	Beauty journal about artistic beauty	Written reflection on 3 experiences of beauty that they have encountered that day that is man-made	Journal listing 3 things observed that day	5–10
**Day 5**	Learning to transfer Aes. Mindset to everyday	Art photography videos focusing on slow and aesthetic looking Beauty Walk	Video of how to focus attention on everyday social interactions and learn about noticing small details Walk to practice observation	20–30
**Day 6,7,8**	Beauty journal	Taking photos or videos of natural beauty they passed during the day	Daily photo journal of descriptive photos of their observations and day life	5–10
**Day 9**	Learning about emotion regulation with beauty	Reading a short text about how beauty can induce positive emotions and with the challenge of reflecting on how beauty has impacted emotions	Reading a text about the importance of observation skills in life, focusing on emotions with the challenge to pay attention to own emotions and aspects of environment that might trigger them	5–10
**Day 10,11,** **12,13**	Practicing emotion regulation with beauty	Daily reflection on how beauty impacted emotions/stress that day. Challenge to stop, find and appreciate beauty when stressed or upset	Daily journal of things that happened that day and how that impacts emotions. Challenge to pay attention to emotions during the day	5–10
**Last day**	Develop beauty seeking behaviour	Making a written plan to add beauty to life. Like taking a trip to encounter beauty or adding beauty to the home	Making a written plan to add something new to their life to continue to practice observation skills	15

### Development of the intervention and control programmes

To prepare for this study, we designed, produced, and validated the intervention procedure. First, we conducted a literature review on past arts and beauty appreciation interventions to glean activity components and learning goals that should be incorporated into our new arts-based beauty appreciation programme. Six studies were identified, finding evidence that appreciation of beauty can be enhanced, that informed our intervention design [25–30]. These studies use multi-week programmes that involve activities aligning with four learning outcomes, including increasing exposure to beauty, learning to notice beauty, cultivating an aesthetic mindset, and reflecting on the worth or utility of beauty. In addressing these aspects, past programmes increased exposure to beauty through, for example, nature walks [25, 26] or adding plants to the house [28, 29]. To increase awareness of beauty—that is, noticing the beauty that is already part of one’s environment—directed attention tasks were used like keeping beauty journals or shooting photos of beauty to increase the habit of being aware of the beauty around them [30]. Past studies included didactic components to cultivate an aesthetic mindset, which focuses on noticing the beauty in objects in addition to their pragmatic purpose [33]. This included learning about how to appreciate mundane objects as beautiful through practice in the classroom-based sessions, for example [27]. Lastly, understanding the worth of beauty was encouraged through reflection exercises about the emotions felt during beautiful experiences [28, 29]. This latter learning goal is linked to how beauty can regulate emotions. However, the authors did not label it as such. Emotion regulation through beauty is a likely mechanism of how beauty appreciation as a skill or trait can impact well-being and mental health outcomes—known as sensory emotion regulation [34]. Having an aesthetic mindset and engaging with beauty have been shown to reduce the impact of distressing images [35], induce positive emotions [36], activate reward networks in the brain (For review see [37]), and is theorised to support distancing and emotional reappraisal [38]—key aspects of emotion regulation [39]. Thus, we developed our intervention programme activities to target these learning goals, as seen in column two of Table 1. The control programme, on the other hand, was designed to mirror the activity components but not activate these learning goals.

After designing the initial intervention and matched control programmes, we conducted a small-scale qualitative study to establish the credibility, feasibility, and comparability of the intervention and control programmes (*N* = 6, 3/condition). Participants completed a condensed version of one of the programmes, which included only one repetition of each activity (see Intervention Description Section). They were asked about feasibility issues, that is, facilitators and barriers to participation, and the effects of the intervention or skills learned in an in-depth semi-structured interview. After informed consent, online interviews were recorded on Microsoft Teams and automatically transcribed and manually checked. Feasibility issues mentioned by participants were addressed in a revision of the programmes, which included adding daily reminders, more explanatory text, and reducing the duration to two weeks instead of the planned three weeks.

The transcripts were coded based on the Braun and Clark six-step method [40] to assess learning outcomes and effects and grouped into themes. Table 2 illustrates the key themes of the intervention and control programmes’ effects or skills developed, notably revealing that feedback regarding the beauty awareness programme centred on appreciating beauty in everyday life, which was previously unnoticed. In contrast, the control programme focused on observation skills and recognising beauty in only picturesque locations. From this pilot study, we concluded that the programmes were comparable in intensity, credibility, and enjoyment and that the control condition did not enhance the appreciation of beauty in mundane spaces and objects.

**Table 2 Tab2:** Comparison of the intervention and control programme effects and learning outcomes

Programme	Theme	Description
Intervention	Art seeking and appreciation	Having a desire to seek out art experiences and appreciate art more deeply and slowly
	Mood boost	Improved mood, motivated and inspired positive behaviour and thoughts
	Noticing mundane beauty	Increased awareness and appreciation of everyday objects and locations and looking beyond obvious sources of beauty
Control	Observation skills/mindfulness	Increased attention towards the environment
	Noticing beauty only in beautiful places	When in a beautiful location, noticing more details in the environment and appreciating them but not noticing more beauty in mundane objects/locations

### Intervention description {11a}

Participants will first visit an art museum (with a free entrance ticket) that they can choose from a pre-selected list of five art museums, with an accompanying audio guide developed as part of the project and instructional video. This guide and video instruct participants to view artworks slowly and to practice their observation and appreciation skills (often called “slow-looking” in museum studies [41]). From there, participants will journal three beautiful things they have encountered that day. Next, participants will be shown video art demonstrating how to observe beauty in small details (such as lentils boiling in water or waving grass), which they will be instructed to practice on a beauty walk. Following this, participants will be encouraged to take photos or videos of beautiful things they see around them in the photographer’s style (zoomed in to almost abstraction). Finally, information about regulating emotions through sensory experiences will be provided with the instruction to practice seeking beauty when stressed or having negative emotions. The information will be a short text about how our sensory experiences, such as appreciating beauty, can help to regulate emotions, summarising the latest research findings on sensory emotion regulation [34]. Finally, participants will be instructed to plan to incorporate more beauty into their lives in a self-made list (i.e. museum trips, taking a more beautiful way home, adding plants to a workspace, choosing seats with lovely views, or going for nature walks).

### Active control description

The active, matched control group will focus on developing pragmatic observation skills that do not focus on cultivating beauty appreciation. Instead, participants will be instructed to pay attention to and identify objects and elements in their surroundings without emphasizing their aesthetic value. For example, they will be asked to pay attention and count objects of the same colour they encounter, notice social behaviour and the people they pass on the street, or the types of buildings and elements in the city. The programme starts with a two-hour tourist trip to their own or a new city. They will receive a video and an audio guide that will guide them in closely observing their environment. Following this, participants will be asked to write a journal about three things they observed that day. Next, they will be shown a video demonstrating how to notice tiny details and improve observation skills, take a wider perspective, and keep track of patterns, following which they can practice on an observation walk.

Participants will practice documenting observations with their cameras. They will then be given a text about how important being observant is, especially being aware of emotions and be asked to report on their daily experiences and emotions. Here, participants will journal about their day and how daily events impact their feelings. This aims to match the intervention aspect of learning to be more aware of emotions. Finally, participants will be asked to make a written list of things they want to add to their lives to continue to practice their observation skills, like visiting a new city, or changing their routine.

### Criteria for discontinuing or modifying allocated interventions {11b}

Allocation groups will not be modified after randomisation.

### Strategies to improve adherence to interventions {11c}

Reminders are sent to participants' mobile phones before and during the two-week programme. Frequent monitoring of participant progress and adherence will be conducted, and participants not completing the programme will be contacted personally by the researcher over email to determine the reason for non-adherence and offer technical support and encouragement if needed.

### Relevant concomitant care permitted or prohibited during the trial {11d}

There are no restrictions on either group, except that the control group is asked not to visit museums or shopping malls (as a cover) during the tourist trip.

### Provisions for post-trial care {30}

There is no provision for post-trial care.

### Outcomes {12}

#### Primary outcome

The primary outcome is beauty appreciation, which will be taken at time points 1, 2, and 3, measured with the Engagement with Beauty Scale Revised (EBS-R) [42, 43], containing 18-item self-report items designed to assess cognitive and emotional engagement with natural beauty, artistic beauty, moral beauty, and beautiful ideas. Participants respond on a 7-point Likert scale, ranging from 1 (very unlike me) to 7 (very much like me). Example items include reflections on physiological responses to natural beauty, the spiritual experience elicited by art, and the desire for personal growth through moral beauty appreciation. Subscales measure engagement with moral beauty (scores 6–42) and the other three domains (scores 4–28), contributing to a total score ranging from 18 to 126. The EBS-R has demonstrated strong internal consistency and test-retest reliability (0.72 after 4 weeks), while its main strength lies in assessing trait appreciation of beauty without including other aesthetic traits, states, or emotions [44].

### Secondary outcomes

Secondary outcomes will be assessed at time points 1, 2, and 3, including mental well-being and psychological distress. Mental well-being will be measured using the Mental Health Continuum Short Form (MHC-SF) [45]. This has 14 items over three subscales: Emotional Well-being, Social Well-being (eudemonic well-being), and Psychological Well-being. The items are scored on a 6-point Likert scale (0–5), then sum-scored.

The Depression, Anxiety, and Stress Scale (DASS-21) [46] will be used to measure psychological distress. The DASS-21 has 21 items divided over three subscales, including Depression, Anxiety, and Stress. The items are assessed using a 4-point Likert scale (0–3), summed together, and then multiplied by two. This results in 3 subscales as well as a total score.

### Tertiary outcomes

Furthermore, we included tertiary outcomes, including emotion regulation, beauty awareness, attention regulation, mindfulness skills, and burnout. All Tertiary outcomes will be taken at time points 1, 2 and 3, except beauty awareness, which will be taken at time points 2 and 3. The Emotion Regulation Strategies for Artistic Creative Activities Scale (ERS-ACA; [47]) will be used with a slight modification to the question stem. The 18-item scale was designed to measure what type of emotion regulation strategies creative activities can facilitate by responding to each item in the context of “when I am engaging in [name creative activity] … I can/feel, it gives/helps/makes me, it boosts/redirects/reaffirms …” on a 5-point Likert scale from strongly disagree to strongly agree. Items can be summed into avoidance strategies (i.e., I can block out unwanted thoughts or feelings), approach strategies (i.e., it makes me reflect on my emotions), and self-development strategies (i.e., it reaffirms my identity). The stem "When I am appreciating beauty…” is used.

In addition, based on Diessner et al. [26], beauty awareness is measured by the question, “Compared to two weeks ago, I notice beauty… 1) much less than before, 2) less than before, 3) the same, 4) more than before, 5) a lot more than before”. Attention regulation will be assessed using the 20-item Attention Control Scale (ACS) [48]. The questionnaire consists of 2 subscales: (1) Attention Focusing and (2) Attention Shifting. The items are assessed on a four-point Likert scale (1-4), and items will be sum-scored. Mindfulness will be assessed using the Five Facet Mindfulness Questionnaire Short Form (FFMQ-15), with 15 items [49], with five facets: (1) Observing, (2) Describing, (3) Acting with awareness, (4) Non-judging, and (5) Non-reactivity [50]. The items are assessed on a five-point Likert scale (1-5) from rarely to always. Scores will be summed for each facet and the total score. Burnout will be measured using the Burnout Assessment Tool–12 (BAT-12), consisting of 12 items [51, 52]. This questionnaire measures burnout with four subscales: (1) Exhaustion, (2) Mental Distance, (3) Emotional Impairment, and (4) Cognitive Impairment [52]. The items are assessed on a five-point Likert scale (1-5), summed to a total score.

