**Tertiary outcomes**			
ERS-ACA (18 items)	x	x	x
Beauty Awareness Question (1 item)		x	x
FFMQ-15 (15 items)	x	x	x
ACS-12 (12 items)	x	x	x
BAT-12 (12 items)	x	x	x
Interview*			x

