### Intervention and control programmes

After finishing the baseline survey and the research materials arrive by post, the participant can access the online programme platform (hosted on Thinkific, an online course-sharing platform) to start the programme. The programme is followed daily for 14 days by logging into Thinkific on their personal phones or computers (see Intervention section for intervention procedure description).

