### Post-survey, follow-up survey and compensation

The post-survey will be sent once participants have completed the 14-day programme. The list of surveys is in Table 3. At this time, participants are reminded that in 4 weeks, they will be sent the final survey and, following its completion, their compensation. Once the participant has completed it, as confirmed by checking the ID codes of the completed surveys, they will be awarded their Dutch online shopping voucher (Bol.com) and research credits.

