## Statistical methods

### Statistical methods for primary and secondary outcomes {20a}

The main analysis will be conducted in two stages. The first is according to the intention-to-treat (ITT) analysis principle [60], with all participants included where possible. This includes dropouts and non-completers of the programmes. Second, we will repeat the analysis Per-Protocol (PP) [60] to gain a clearer picture of the intervention-related effects, excluding non-completers or poor-quality data (see exclusions below). To evaluate whether there are differences between the conditions at the post-test, considering baseline differences, a series of ANCOVAs with the condition as the IV and the post-test as the DV, with baseline scores, sex, and age as covariates will be run on primary and secondary outcomes. To evaluate the long-term effects of the intervention and the control condition, linear mixed models (LMM) will be fitted to predict each outcome variable. The same approach will be applied to evaluate the tertiary outcomes.

For more details, see our pre-registration: osf.io/q8c6u.

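### At the 4-week follow-up the beauty-awareness item looks back only two weeks, to a point after the programme ended, so it cannot show whether a gain lasted

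*Protocol article*

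**What the plan says.** Under Tertiary outcomes, the protocol article measures beauty awareness with one question whose stem is "Compared to two weeks ago, I notice beauty". It has five answers, from much less (1) through unchanged (3) to a lot more (5). All tertiary outcomes are taken at three time points, "except beauty awareness, which will be taken at time points 2 and 3". Table 3 agrees: the row "Beauty Awareness Question (1 item") is marked at T2 and T3 only. No other stem is given for T3.

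The timing is set in two later sections. Under Intervention and control programmes: "The programme is followed daily for 14 days". Under Post-survey, follow-up survey and compensation: "The post-survey will be sent once participants have completed the 14-day programme", and then "At this time, participants are reminded that in 4 weeks, they will be sent the final survey". The section on the qualitative interviews also places follow-up four weeks after the intervention.

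Statistical methods {20a} plans an ANCOVA at post-test with the baseline score, sex and age as covariates, and linear mixed models for long-term effects. It then adds: "The same approach will be applied to evaluate the tertiary outcomes".

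**The concern.** A change question measures change from its own reference point. Here that point is a fixed distance back from the survey, so it moves when the survey moves. At T2 the two-week look-back spans the programme. At T3 the same words span a fortnight in which no programme was running. The two answers share a label and a scale but describe different intervals.

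The article sends tertiary outcomes through the same long-term model as the other outcomes. Treated that way, a T3 result near the middle of the scale in both arms could be taken to mean that the trained noticing had worn off, when it is equally what full retention would produce. Learning to notice beauty is one of the four learning outcomes behind the programme (Development of the intervention and control programmes), so a wrong reading would bear on a skill that the programme sets out to train.

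**Working it through.** **Inputs, all from the protocol article.** Programme: days 0 to 14. T2: on completion, about day 14. T3: four weeks (28 days) after T2. Look-back in the stem: 14 days.

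**Reference day = survey day − 14.**
- T2: 14 − 14 = day 0, the start of the programme.
- T3: 14 + 28 = day 42, and 42 − 14 = day 28. That is 28 − 14 = 14 days after the programme ended.
- To reach the state before the programme, the T3 look-back would have to be 42 days, about six weeks.

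**Does a late finisher change this?** Suppose a participant takes *k* extra days to finish. T2 is at day 14 + *k* and refers to day *k*, slightly after the start. T3 is at day 42 + *k* and refers to day 28 + *k*, still 14 days after that participant's last programme day. Answering T3 late moves the reference point further from the programme.

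**What the item returns.** Let L(t) be the level of noticing beauty at day t relative to before the programme, and *g* > 0 the gain at day 14. Read literally, the item reports L(14) − L(0) at T2 and L(42) − L(28) at T3. A stem anchored before the programme would report L(42) − L(0) at T3.

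| Course after the programme | L(14) | L(28) | L(42) | T2 item | T3 item as printed | T3 item anchored before the programme |
|---|---|---|---|---|---|---|
| Gain fully kept | g | g | g | +g | 0 | +g |
| Gain lost before day 28 | g | 0 | 0 | +g | 0 | 0 |
| Never gained | 0 | 0 | 0 | 0 | 0 | 0 |
| Half lost between days 28 and 42 | g | g | g/2 | +g | −g/2 | +g/2 |

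A value of 0 corresponds to answer 3. The first three rows differ completely in what they say about persistence, yet give the same T3 answer. The fourth row gives a negative T3 answer although the participant is still above the starting level.

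**Consequence for the planned models.** A mixed model over T2 and T3 would treat L(14) − L(0) and L(42) − L(28) as two readings of one outcome, which they are not. Separately, an ANCOVA with a baseline score cannot be run as described on an item that has no T1 value. The same holds for the pre-post Reliable Change Index that the section on additional analyses {20b} plans for tertiary outcomes.

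**The case against.** The strongest objection is about weight. This is one item in the lowest outcome tier. H1 to H3 concern only the primary and secondary outcomes, and H4 only their moderation by sensory processing sensitivity. Persistence is tested in H3 with the EBS-R, MHC-SF and DASS-21, all taken at all three time points. The T2 reading of the item is sound. The interviews after T3 also ask about effects and learning outcomes, so the item is not the trial's only source on noticing beauty. All of this stands and keeps the point small.

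A second objection is that respondents may not read the stem literally. The answer options refer only to an unspecified earlier time, so some participants may think back to before the programme. This also stands, but it does not rescue the item: T3 would then mix two reference points in unknown proportions.

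A third is that an article condenses the survey and a different T3 stem may have been fielded. That is possible. The article prints this stem, however, and in the same section reports the change it made to the stem of another scale, while giving no T3 variant here. If one was used, stating it settles the matter.

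A fourth is that a change rating carries its reference within it, so the lack of a T1 value is natural, and dropping a covariate that does not exist is ordinary analysis detail. That is fair; the baseline covariate is a minor side point.

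**Conclusion.** The point holds for the T3 use of the item. With the printed stem and schedule, T3 measures change from about day 28 to about day 42. It cannot separate a kept gain, a gain lost before day 28 and no gain, and it should not enter a long-term model together with T2. The timing follows from the article's own dates; the answers in the table assume that participants apply the two-week reference literally.

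Three stronger readings are tempting and are not supported:
- A reader might infer that the T3 difference between arms must be zero whenever the effect lasts. That needs every respondent to read the stem literally and the control arm to be steady from day 28 to day 42. The article secures neither.
- A reader might infer that any fading would put the intervention arm below control. Only fading between about day 28 and day 42 would do so; earlier fading gives no difference.
- A reader might infer that the trial cannot show lasting effects. H3 rests on other measures, and neither it nor the sample size depends on this item.

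**What to change.** Leave the T2 stem unchanged. It already refers to the start of the programme, and changing it while the trial is recruiting would split valid data.

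At T3, use a fixed reference, for example: *Compared to before you started the programme, I notice beauty…*

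Report T3 answers already collected with the two-week stem separately, as change over the last two weeks. Do not model them with T2 or interpret them as persistence.

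Compare the arms at each time point without a baseline-score covariate, keeping age and sex, and say in the analysis text that this item is an exception to the common approach.

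The change is one line in one survey and a sentence in the analysis text. It has two costs: T3 answers from before and after the change cannot be pooled, and the new stem asks participants to recall their noticing of about six weeks earlier. According to Trial status, recruitment was planned to run from November 2024 to June 2025. If all T3 surveys are already in, the reporting and analysis changes can still be made.
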